**Fig. 1 Fig1:**
[figure not shown]
Study flowchart

**Fig. 2 Fig2:**
[figure not shown]
The SPIRIT figure of enrolment, intervention, and assessment

### Adverse events

Previous studies have shown few advert events of sound therapy. A major possible side effect might be hearing damage caused by the excessive volume of the sound. In this study, we set a strict maximum playback intensity limit to make sure all therapeutic sounds are absolutely less than the discomfort loudness threshold. Besides, our project provides the entire audiology tests for tinnitus match, offering in time pure-tone audiometry (PTA), acoustic immittance (AI) test, and other relevant measurements, along with the independently designed audio processing software/APP and meticulous guidance from our otolaryngologists, whereby the potential injuries could be effectively minimized, and timely intervened.

### Sample size calculation

The study sample size was based on the THI scale (the primary outcome), which is used to assess the severity and treatment effect of tinnitus. Considering an 80% effective rate, 5% significance level, 80% power, 30% dropout, and 1:1 grouping, a total sample of 68 (34 per group) will be required.

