**Methods and analysis:**

A randomized, double-blinded, controlled, clinical trial will be carried out. Sixty-eight patients with subjective tinnitus will be recruited and randomly allocated into two groups in 1:1 ratio. The primary outcome is Tinnitus Handicapped Inventory (THI); the secondary outcomes are the Hospital Anxiety and Distress Scale (HADS; HADS subscales for Anxiety (HADS-A) and Depression (HADS-D)), Athens Insomnia Scale (AIS), the visual analog scale (VAS) for tinnitus, and tinnitus loudness matched by sensation level (SL). Assessment will be performed at baseline and at 1, 3, 9, and 12 months post-randomization. The sound stimulus will be persistent until 9 months after randomization, and be interdictory in the last three months. Data collected during the intervention process will be analyzed and compared to baseline.

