### Outcome measures

#### Primary outcome

##### Tinnitus Handicap Inventory (THI)

THI is a self-assessment inventory to quantify the impact of tinnitus on everyday function. It includes 25 items to evaluate the functional, emotional, and catastrophic response reactions to tinnitus. The answer options for each question include “yes,” “sometimes,” and “no.” Answering “yes” gets 4 points, answering “sometimes” gets 2 points, and “no” gets 0 points. Add the scores of the 25 questions in the above three categories to get the THI score. The score quantifies the patient’s tinnitus disability into 5 levels: slight (0–16), mild (18–36), moderate (38–56), severe (58–76), and catastrophic (78–100). The higher the score, the more severe tinnitus is. The results of THI will not be affected by age, gender, or hearing loss, having good internal consistency reliability and construct validity.

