### Data analysis

Data analysis will be conducted via statistical software STATA, V. 15.0. The differences in time-varying outcomes between UM and MTRS groups are compared by generalized estimating equations (GEE), which is classified as one sort of generalized linear model (GLM). Subsequently, concomitant variables, including demographic variables, disease data, and tinnitus matching test data at T0, will be weighted and controlled, to further analyze the affecting factors of acoustic therapy for tinnitus. *P* < 0.05 is considered statistically significant and data are presented as means ± standard deviation (SD). All expulsion/withdrawal cases are classified into intention to treat (ITT), in which the miss values would be filled by the method of imputation obtained from the last observation. Meanwhile, per-protocol sets (PP) analysis will be conducted. Finally, compare the ITT and PP results.

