A few potential issues related to current RCT should be addressed carefully. This trial has a time-consuming follow-up period, totally having 5 timepoints (when participants are allocated and 1, 3, 9, and 12 months after commencing treatment) for investigators to collect trial data, as a result, there unavoidably will be some participants withdraw from our trial due to different reasons. To reduce the follow-up loss to the maximum, we keep in touch with all participants and timely resolve their encountered problems through multiple ways, such as phone calls, WeChat, and email. Moreover, data input of the assessment scales should avoid manual input errors, by which the electronically input/recording and online submitting will be preferentially adopted, and recorded data will be gathered and exported into statistical analysis software in the background. Also, one assigned investigator will examine the imported data that coming from the CRF (case report form) paper table and dispose of the relevant mistakes or omissions in time.

In conclusion, our trial will concretely and detailly provide the clinical evidence for acoustic therapy by the randomized controlled comparisons between our patented MTRS and UM. Based on preliminary observation and clinical experiences, we hypothesize that the effects of MTRS will be superior to those of UM in terms of the aforementioned outcome measurements and assessment scales. Specifically, we expect that participants in the MTRS group will experience more significantly reduced THI scores, lessened AIS and VAS scores, and better subjective tinnitus relief.

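### The 80% power claimed for N = 68 cannot be reproduced from a single 80% effective rate, nor shown to apply to the planned THI score comparison

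*Protocol article*

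**What the plan says.** The Sample size calculation section ties N to the primary outcome: "The study sample size was based on the THI scale (the primary outcome". Its only effect input is one rate: "Considering an 80% effective rate, 5% significance level, 80% power, 30% dropout, and 1:1 grouping, a total sample of 68 (34 per group". It names no arm for that rate, no comparator rate, no difference and no SD, and it does not say whether the 5% is one- or two-sided.

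Elsewhere the article treats THI as a score:

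- Primary outcome section: "Add the scores of the 25 questions in the above three categories to get the THI score". The range is 0–100 with five severity levels. No cut-off or change is defined as effective.
- Introduction: the research hypothesis is that scale scores will be lower with MTRS than with UM.
- Data analysis section: "The differences in time-varying outcomes between UM and MTRS groups are compared by generalized estimating equations (GEE", with data summarised as mean and SD.
- Discussion: the expected result is that "participants in the MTRS group will experience more significantly reduced THI scores".

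**The concern.** A two-group superiority calculation needs two rates, or a mean difference and an SD. With one rate, N is not determined, so a reader cannot tell what effect the trial was sized to find. The rate is also a different kind of quantity from the one to be analysed: a proportion of responders against a mean score followed over time.

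At stake is how the result will be interpreted. A reader who sees 80% power will assume it refers to a plausible THI difference. If it refers to a very large effect, or to an unanalysed responder rate, a non-significant result carries less information than the stated power suggests.

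**Working it through.** **Inputs from the article.** Rate 0.80; significance level 0.05 (taken as two-sided); power 0.80; dropout 30%; allocation 1:1; N = 68, or 34 per arm. After 30% loss, 34 × 0.7 = 23.8, about 24 per arm.

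**Step 1: read the 80% as a proportion.** Pooled two-proportion formula, with p1 = 0.80 and p2 the unknown UM rate:

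n = [1.960·√(2p̄(1−p̄)) + 0.842·√(p1(1−p1) + p2(1−p2))]² / (p1−p2)²

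Example with p2 = 0.41: p̄ = 0.605, so n = [1.960 × 0.691 + 0.842 × 0.634]² / 0.39² = 3.567 / 0.1521 = 23.5, i.e. 24 per arm.

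| Assumed UM rate | Evaluable per arm | Total after n/0.7 |
|---|---|---|
| 0.40 | 23 | 66 |
| 0.41 | 24 | 70 |
| 0.50 | 39 | 112 |
| 0.60 | 82 | 236 |
| 0.70 | 294 | 840 |

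Solving backwards for the UM rate that gives 80% power:

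- 41.3% at 23.8 per arm (dropout applied as n/0.7);
- 43.0% at 26 per arm (dropout applied as n × 1.3; 26 × 1.3 = 33.8, so 34);
- 47.9% at 34 per arm (dropout ignored).

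One-sided, unpooled and continuity-corrected variants that allow for dropout put totals within two of 68 at UM rates of about 36% to 48%. The article states none of these rates. As an illustration only, 80% against an assumed 60% has 32% power with 24 per arm and 43% with 34.

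**Step 2: read the 80% as a standardised difference of 0.8.** A two-sided two-sample t-test at 5% and 80% power needs 25.5, so 26 per arm.

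- 26 × 1.3 = 33.8, so 34 per arm and 68 in total. This matches the stated N exactly.
- Multiplying by 1.3 does not preserve 26 after 30% loss. That would take 26 / 0.7 = 37.1, so 38 per arm and 76 in total.
- With about 24 per arm left, power for d = 0.8 is 77%; with all 34 it is 90%.

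**Step 3: what N = 68 can detect on the THI score.** Unadjusted t-test at one timepoint, 80% power, two-sided 5%. The normal approximation d = (1.960 + 0.842)·√(2/n) gives 0.81 at n = 24 and 0.68 at n = 34. The exact t-test gives 0.83 and 0.69. The article gives no THI SD, so those below are assumptions.

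| Per arm | Detectable d | SD 15 | SD 20 | SD 25 |
|---|---|---|---|---|
| 24 | 0.83 | 12 points | 17 points | 21 points |
| 34 | 0.69 | 10 points | 14 points | 17 points |

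**The case against.** The strongest counter-argument is Step 2. The article says the size was based on THI, and a standardised difference of 0.8 returns 68 exactly. The phrase may be a mistranslated effect size, in which case the power does refer to a THI mean difference. This reading cannot be excluded, so the documents do not support the stronger inference that the power belongs to a different endpoint. What remains is that the wording is then wrong, 0.8 SD is a large effect offered without justification, and the dropout allowance leaves power slightly below 80%.

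Second, this is a condensed article, and the Ethics and disseminations section says a full protocol is available on request. A second rate or an SD may be given there, so its absence alone would be no finding. The point rests instead on the mismatch between the rate given as the basis for N and the score comparison described in the same article.

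Third, the Data analysis section keeps withdrawals in the ITT set with the last observation carried forward, so up to 34 per arm enter that analysis, and GEE uses several visits. This is fair, and it is why both 24 and 34 are shown. Carrying values forward does not restore the lost information, so 34 is the favourable end of the range. Repeated measures or baseline adjustment could lower the detectable difference, by an amount that depends on correlations the article does not give.

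Fourth, the 60% rate and the SDs above are illustrative assumptions, not the sponsor's figures.

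**Conclusion.** The point holds in this form: 68 does not follow from the stated inputs, and the stated 80% power cannot be shown to apply to the comparison of THI scores. As a proportion, the calculation needs an unstated UM rate of about 41–43%, a gap of 37–39 percentage points (48%, a gap of 32, if dropout is ignored). As a standardised difference of 0.8, the number is reproduced but the label is wrong, and power after the planned dropout is 77%.

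On the score itself, N = 68 has 80% power for 0.83 SD with 24 per arm or 0.69 SD with 34, in an unadjusted single-timepoint comparison. Conversion to points rests on an assumed SD.

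A reader might also infer that the trial is underpowered for a relevant benefit, or that a null result will be presented as no benefit. The documents support neither: they give no target THI difference or SD to judge against, the design is superiority, and nothing says how a null result will be worded.

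**What to change.** Keep N = 68. In the Sample size calculation section, delete the effective rate or correct it: if it was a standardised difference, say so; if it was a responder proportion, define the responder, give both rates and name the matching analysis.

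Then state the sensitivity for the planned outcome, for example: with 68 randomised, an unadjusted comparison of THI at one named timepoint has 80% power at two-sided 5% to detect 0.83 SD if 24 per arm remain after 30% dropout, or 0.69 SD if all 34 per arm contribute. Convert this to THI points with a stated and sourced SD. Label it as what N = 68 can detect, not as how N was originally derived. Add that a non-significant result will be reported by its confidence interval.

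The cost is rewording and a less favourable stated sensitivity. No extra patients or procedures are needed.

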### Data analysis

Data analysis will be conducted via statistical software STATA, V. 15.0. The differences in time-varying outcomes between UM and MTRS groups are compared by generalized estimating equations (GEE), which is classified as one sort of generalized linear model (GLM). Subsequently, concomitant variables, including demographic variables, disease data, and tinnitus matching test data at T0, will be weighted and controlled, to further analyze the affecting factors of acoustic therapy for tinnitus. *P* < 0.05 is considered statistically significant and data are presented as means ± standard deviation (SD). All expulsion/withdrawal cases are classified into intention to treat (ITT), in which the miss values would be filled by the method of imputation obtained from the last observation. Meanwhile, per-protocol sets (PP) analysis will be conducted. Finally, compare the ITT and PP results.

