Based on the accumulated explorations on the relevant background and our clinical experience in tinnitus diagnosis and treatment, we presume that customized acoustic therapy, coupled with tinnitus-specific psychological counseling, might be powerful for persistent tinnitus relief. Therefore, we designed a new treatment system, optimizing the education counseling and introducing a customized relieving sound therapy model that is designated as MTRS. Our method has been authorized by China National Invention patent (ZL201510165976.9). To verify the safety and clinical efficacy of MTRS, we are conducting the current randomized controlled clinical study: participants in the control group receive the unmodified music (UM) treatment, while subjects in the experimental group will be given the MTRS treatment, and all participants should accept the follow-up visit at regular intervals to supervise the tinnitus variation. Our research hypothesis is that the scores of tinnitus evaluation scales of the MTRS group are significantly lower than that of UM group, whereby our current trial could provide the corresponding clinical evidence.

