### Timepoints of follow-up

There are total 5 timepoints, including the baseline when participants are allocated and 1, 3, 9, and 12 months after commencing treatment, for investigators to collect data of multi-dimensional assessment scales (THI, HADS, AIS, VAS, SL). In detail, follow-up evaluations/tests will be conducted during acoustic therapy at 1, 3, 9 months after commencing treatment, whereby the short-term and long-term treatment effects of MTRS will be comprehended. In order to verify the long-term and lasting effect of current therapy, all acoustic stimulation will be withheld from participants during 10 to 12 months after commencing treatment. Thus, the final time to gather follow-up evaluation/test data is 12 months after commencing treatment. Additionally, the data collection method, whenever during therapy, must be consistent in the way the investigator collects the baseline data at the beginning of this trial. Tinnitus match tests are proper approaches for analysts to know the frequency and loudness variations of tinnitus, which must be conducted at both the initial point (baseline data collection) and endpoint (12 months after commencing treatment). Any qualified study cases should meet these criteria: baseline data completion at the initial timepoint (T0), research data collection at 1, 3, 9, and 12 months after commencing treatment timepoints (T1, T2, T3, T4 nodes, respectively, during trial). Midway quitting and loss to follow-up will be recorded.

The study flow diagram is shown in Fig. 1, and the SPIRIT figure involving enrollment, intervention, and assessment is presented in Fig. 2.

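### No primary visit or GEE contrast is fixed for THI, and the main group comparison as written has no baseline THI term

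*Protocol article*

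**What the plan says.** - **Outcome and visits.** The abstract states "The primary outcome is Tinnitus Handicapped Inventory (THI") and "Assessment will be performed at baseline and at 1, 3, 9, and 12 months post-randomization". Neither the abstract nor the Primary outcome section ties THI to a visit.
- **Treatment state at each visit.** Months 1, 3 and 9 fall during sound therapy. Before the last visit, "all acoustic stimulation will be withheld from participants during 10 to 12 months after commencing treatment" (Timepoints of follow-up). That section uses the on-treatment visits for short- and long-term effect and month 12 for the lasting effect. It ranks none above the others.
- **Main analysis.** "The differences in time-varying outcomes between UM and MTRS groups are compared by generalized estimating equations (GEE"), with P < 0.05 as the criterion (Data analysis). No multiplicity rule across visits is given.
- **Covariates.** As a subsequent step, "concomitant variables, including demographic variables, disease data, and tinnitus matching test data at T0, will be weighted and controlled", and the purpose is "to further analyze the affecting factors of acoustic therapy for tinnitus". Baseline THI is collected from everyone before allocation (Procedure) but is not named in this list.
- **Scale.** The Introduction's hypothesis is that "the scores of tinnitus evaluation scales of the MTRS group are significantly lower than that of UM group". The abstract says "Data collected during the intervention process will be analyzed and compared to baseline". The Discussion expects a larger THI reduction under MTRS.

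**The concern.** A primary outcome measured four times after baseline does not define one claim until a visit, or a way of combining visits, is chosen. Here the choice changes the question: effect at the end of therapy, effect three months after stopping, or a mixture. If it stays open until the data are seen, a positive result at one visit can be presented as the trial's result, and a reader cannot tell how many other contrasts were available.

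The second part is precision. Baseline THI is likely to be among the strongest predictors of later THI, and it is already collected. With 34 patients per arm, chance imbalance at baseline matters. The main comparison as described does not use baseline THI as a covariate, and the step that brings covariates in serves a different purpose.

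**Working it through.** There is no figure in the plan to reproduce on this point. The sample size of 68 rests on an 80% effective rate with no visit attached, so it does not identify a primary contrast either.

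**Inputs from the protocol article:** 34 per arm (Randomization and allocation; Sample size calculation), four post-baseline visits (Timepoints of follow-up), significance level 0.05 (Data analysis). **Assumed, because the document gives no THI correlations or SD:** between-visit correlation 0.5-0.8, and correlation r between baseline and follow-up THI of 0.5-0.7.

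**1. What the GEE could be testing.** Each reading below fits the Data analysis section.
- *Average group effect over the four follow-up visits:* one test, 5% error. The estimand is (d1 + d3 + d9 + d12)/4, where d is the group difference at that month. It equals the 9-month effect only if the four differences average to d9, for instance if the effect is constant through build-up and withdrawal.
- *Group main effect with T0 as a fifth response:* one test, but with no expected difference at T0 and a constant later effect d, the estimand is (0 + 4d)/5 = 0.8d.
- *Joint group-by-time test:* one test, 5% error. It shows that profiles differ, not when.
- *Visit-by-visit contrasts:* four tests at 0.05.

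**2. Error rate under visit-by-visit testing.** With independent tests, 1 - 0.95^4 = 18.5%, an upper reference. Simulating four equicorrelated normal statistics under the null (1,000,000 draws, two-sided) gives:

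| Between-visit correlation (assumed) | Chance of at least one P < 0.05 |
|---|---|
| 0.5 | 15.6% |
| 0.6 | 14.4% |
| 0.7 | 13.1% |
| 0.8 | 11.4% |

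**3. What baseline adjustment is worth at a single visit.** In units of the THI variance, with equal variances at baseline and follow-up: unadjusted score 1; change score 2(1 - r); adjusted 1 - r^2. The ratio of change to adjusted variance is 2(1 - r)/(1 - r^2) = 2/(1 + r).

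| r (assumed) | Change | Adjusted | Cut against unadjusted score | Change / adjusted |
|---|---|---|---|---|
| 0.5 | 1.00 | 0.75 | 25% | 1.33 |
| 0.6 | 0.80 | 0.64 | 36% | 1.25 |
| 0.7 | 0.60 | 0.51 | 49% | 1.18 |

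A single-visit comparison with 80% power on unadjusted scores would have about 90% power after adjustment at r = 0.5 and 94% at r = 0.6.

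**4. Chance baseline imbalance.** The standard error of the baseline difference between arms is sqrt(2/34) = 0.243 SD. In an unadjusted score comparison, a fraction r of any such difference is expected to reappear at follow-up.

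**5. Averaged contrast.** Under compound symmetry at r = 0.6, the unadjusted four-visit mean has variance (1 + 3 x 0.6)/4 = 0.70, and the adjusted mean 0.70 - 0.36 = 0.34. The adjusted single visit has 0.64. So moving from an unadjusted average to an adjusted single visit gains little precision (0.70 to 0.64). The gain comes from adjusting within whichever contrast is chosen.

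**The case against.** The strongest reply is that this is a condensed article, and that the parameterisation and covariate set of a GEE belong in an analysis plan that is not shown. That holds for the working correlation, coding and similar detail. It does not hold for the time point or contrast of the primary outcome, which defines what the trial claims. The article describes both visits and analysis, and still leaves this open.

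Three stronger readings are tempting, and the text does not support them.

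- *That raw scores are analysed.* The Introduction speaks of lower scores, but the abstract and the Discussion use the language of change. The scale is not fixed, so the 25-49% figure applies to one reading only.
- *That baseline THI is excluded.* The article does not say so. T0 is one of the five timepoints. If it is a response in the GEE and group-by-time is tested, baseline is already used and the imbalance argument falls away. Disease data in the covariate list might also include THI, though it would then enter only at the later step.
- *That four tests at 0.05 are planned.* No visit-by-visit testing is described. The 11-16% belongs to a procedure that the text permits, not one that it states. It cannot be added to the dilution under an averaged effect, because those are alternative readings.

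It is also fair to say that the document does not rank month 9 above month 12. A pre-specified averaged or joint contrast would control the error rate equally well. How far an average departs from the 9-month effect depends on an effect pattern that the document does not give.

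**Conclusion.** The point holds in this form: the protocol fixes no primary visit or contrast for THI across three on-treatment visits and one off-treatment visit, does not settle scores against change, and describes a main comparison with no baseline THI term. The first part carries the weight and should be fixed before the data are analysed, because it determines the claim. It rests on the text alone.

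The sizes are conditional. The inflation to about 11-16% needs visit-wise testing and assumed correlations of 0.8-0.5. The precision loss at a single visit is 25-49% of the variance if unadjusted scores are used, or a variance 1.33 to 1.18 times the adjusted one if change scores are used, both at assumed r = 0.5-0.7. If the intended model already takes T0 as a response with a group-by-time test, much of the precision loss disappears, but the missing contrast remains.

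**What to change.** - Include baseline THI, interacting with visit, in the primary GEE, or use a model that takes T0 as a response with the two arms constrained to a common baseline mean. State this as part of the primary analysis, and give each secondary outcome its own baseline value.
- Pre-specify one primary THI contrast. One defensible choice is the group difference at 9 months, the end of therapy, from a group-by-visit model. The 12-month off-treatment difference is then tested at 0.05 only if the 9-month test is significant. Another contrast would also serve if it is named in advance and its mixture of treatment states is acknowledged.
- Report the remaining visits as supportive estimates with confidence intervals, and keep the other covariates in the exploratory step.
- Use the same scale of comparison in the abstract, hypothesis, analysis and discussion.

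The cost is protocol and analysis-plan wording. The THI data needed are already to be collected at every visit. The one real downside is that the claim is tied to one contrast, even if another visit looks better.

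### Last-observation imputation is the only stated ITT rule for missing data; it carries baseline or on-therapy THI scores into the off-therapy 12-month visit and can bias that contrast in either direction

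*Protocol article*

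**What the plan says.** All statements are in the protocol article.

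- **Data analysis**, analysis set: "All expulsion/withdrawal cases are classified into intention to treat (ITT").
- **Data analysis**, missing values: "in which the miss values would be filled by the method of imputation obtained from the last observation". This is single imputation by last observation carried forward (LOCF). No other missing-data method is named.
- **Data analysis**, model: "The differences in time-varying outcomes between UM and MTRS groups are compared by generalized estimating equations (GEE").
- **Data analysis**, companion analysis: "Meanwhile, per-protocol sets (PP) analysis will be conducted. Finally, compare the ITT and PP results".
- **Timepoints of follow-up**: THI is collected at baseline and at 1, 3, 9 and 12 months. The visits at 1, 3 and 9 months are during therapy. Then "all acoustic stimulation will be withheld from participants during 10 to 12 months after commencing treatment", and the stated reason is "In order to verify the long-term and lasting effect of current therapy".
- **Sample size calculation**: "80% power, 30% dropout, and 1:1 grouping", for 68 participants in total.
- **Withdrawal/retention of participants**: loss to follow-up is named as a technical difficulty, and too little daily listening is an example of a recorded withdrawal reason.

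**The concern.** The 12-month visit differs in kind from the other follow-up visits: it is the only one after sound has been withdrawn, and it exists to show whether any benefit persists. For a participant lost after month 9, LOCF enters the month-9 score, taken during therapy, as the month-12 score. That assumes the answer to the question the visit asks. For a participant lost earlier, it enters a month-3, month-1 or even baseline score.

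Two things are at stake. First, the 12-month group difference can be wrong: too large if benefit fades after the sound stops, too small if benefit builds up over time and participants leave early. Second, the analysis treats imputed scores as measured, so it reports more precision about month 12 than the trial has. Because low listening time is a recorded withdrawal reason, dropout may be related to treatment and may differ between arms.

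The rule is written into the article, so this is not a detail left to an analysis plan that is not shown.

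**Working it through.** **Inputs from the article.** N = 68 (34 per arm); dropout 30%; visits at 0, 1, 3, 9 (on therapy) and 12 months (off therapy); LOCF in the ITT set. The figure of 68 cannot be reproduced, because no comparator rate is given. That is a separate matter; only the 68 and the 30% are used here.

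**Inputs that are assumed.** The article gives no THI means, SD, within-patient correlation or timing of dropout. All of these are assumptions below.

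**Step 1, scale.** 0.30 × 68 = 20.4, so about 20 participants (about 10 per arm) would have an imputed 12-month score and about 48 an observed one.

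**Step 2, formula.** Let d_j be the true benefit (UM minus MTRS, THI points) at visit j, and p_j the proportion last seen at visit j, equal in both arms and unrelated to outcome. Then

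- LOCF 12-month benefit = Σ p_j d_j + (1 − Σ p_j) d_12
- bias = Σ p_j (d_j − d_12)

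**Step 3, illustration.** Take d = 0, 5, 10, 15 at months 0, 1, 3, 9 and p = 5%, 5%, 10%, 10%, so that 70% are seen at month 12.

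- Benefit gone by month 12 (d_12 = 0): 0.05×0 + 0.05×5 + 0.10×10 + 0.10×15 + 0.70×0 = **2.75**; truth 0.
- Benefit lasts (d_12 = 15): 2.75 + 0.70×15 = **13.25**; truth 15.

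The same rule overstates in one case and understates in the other.

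**Step 4, dependence on timing.** Take a 12-point benefit at month 9 with all 30% lost after month 9. If it has gone by month 12, LOCF gives 0.30×12 = 3.6 where the truth is 0. If it is still 12 at month 12, LOCF gives 0.30×12 + 0.70×12 = 12, with no bias. In simulation (1,500 trials, 34 per arm, baseline-adjusted 12-month comparison, assumed SD 20 and correlation 0.6, dropout completely at random), the false-positive rate in the first of these cases was 11.9% instead of 5%. With dropout spread evenly over visits, the apparent benefit was 1.8 points and the rate 6.6%.

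**Step 5, identical arms.** If the arms have the same mean at every visit and equal dropout, every d_j is 0 and so is the bias. With 40% dropout in UM and 20% in MTRS, spread evenly, and assumed means of 50, 44, 40, 36, 42 in both arms, the bias (MTRS minus UM) is (0.05 − 0.10) × [(50−42) + (44−42) + (40−42) + (36−42)] = −0.05 × 2 = −0.1 point.

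**Step 6, precision.** With SD 20 and correlation 0.6, the baseline-adjusted residual SD is 20 × √(1 − 0.6²) = 16. With 34 scores per arm the standard error is 16 × √(2/34) = 3.9. With 0.70 × 34 = 23.8 observed per arm it is 16 × √(2/23.8) = 4.6. In the simulations with 30% dropout in each arm, LOCF gave average standard errors of about 3.7 to 4.3, against about 4.7 from observed 12-month scores, which is 9% to 21% smaller. LOCF thus reports roughly the precision of a trial without dropout.

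**Step 7, a contrast over all visits.** With the Step 3 inputs, LOCF also alters the earlier visits: month 1, 0.95×5 = 4.75; month 3, 0.90×10 + 0.05×5 = 9.25; month 9, 0.80×15 + 0.10×10 + 0.05×5 = 13.25. The equally weighted mean over the four follow-up visits is:

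| Case | LOCF | Truth |
|---|---|---|
| Fading benefit | (4.75 + 9.25 + 13.25 + 2.75)/4 = 7.5 | (5 + 10 + 15 + 0)/4 = 7.5 |
| Lasting benefit | (4.75 + 9.25 + 13.25 + 13.25)/4 = 10.125 | (5 + 10 + 15 + 15)/4 = 11.25 |

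In the fading case, errors of opposite sign at single visits happen to cancel. The 12-month figures therefore cannot be read as the bias of an overall GEE effect.

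**The case against.** Several objections have force and limit the point.

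- **Bias is not certain.** Step 4 (difference flat from month 9 to 12, all dropout late) and Step 5 (identical arms, equal dropout) give none. A reader might infer that LOCF necessarily biases the ITT result, or that it favours MTRS; the documents support neither.
- **The primary contrast may not be the 12-month one.** The article states no primary time point, and the GEE uses all visits. As Step 7 shows, the bias of an all-visit contrast can be smaller or different.
- **Unequal dropout alone.** A reader might infer that unequal dropout by itself creates a sizeable false difference. That depends entirely on the assumed course of THI, for which the article gives no means; the course in Step 5 yields only 0.1 point.
- **The per-protocol analysis is a partial check.** The article calls cases qualified if they have data at all five timepoints. If these form the per-protocol set, which it does not say, observed 12-month scores would be used, and under random dropout the two analyses should diverge when LOCF is biased. So one cannot say the comparison would never show the problem. But 34 per arm makes it imprecise, the subset is selected, and a discrepancy would not say what the ITT answer is.
- **Scope.** The 30% is a planning allowance, not an observed loss. The sentence concerns withdrawn participants and is silent on intermittent gaps. Not every carried score is truly on therapy, since some are baseline scores and some participants may already have stopped listening.
- **Size.** A bias of 2.75 points is below the standard error of about 4.7. In the simulations with identical arms, LOCF's false-positive rate was about 4%, so the excess false positives come from the bias and not from the smaller standard error alone.

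None of this makes LOCF a suitable sole rule when the last visit is deliberately off therapy.

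**Conclusion.** The concern holds in this form: the only stated ITT rule carries scores across the planned stop of therapy, assumes the persistence that the 12-month visit is meant to test, and counts imputed scores as data. With 30% dropout it can bias the 12-month difference in either direction. In the Step 3 illustration the bias is +2.75 points if benefit fades and −1.75 points if it lasts (13.25 against 15). The standard error is also too small for what is known about month 12.

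The 68, the 30% and the visit schedule come from the article; trajectories, dropout timing, SD and correlation are assumptions, so the figures show mechanism and order of size, not a forecast. The conflict between the imputation rule and the purpose of the last visit does not depend on them.

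**What to change.** In Data analysis, replace last-observation imputation as the ITT rule with one of the following:

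- multiple imputation by arm, using baseline and all observed THI scores, before the planned GEE; or
- a likelihood-based repeated-measures model on all observed THI values, with group-by-visit terms and baseline THI.

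State that no score from month 9 or earlier is carried into month 12. LOCF may remain as a labelled sensitivity analysis. Both replacements assume that data are missing at random. The covariance structure, the degrees-of-freedom method and sensitivity analyses for departures from that assumption can be left to the statistical analysis plan; their absence from the article is not part of this finding.

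Cost: an amendment to the wording, which by the article's own rule needs ethics review, and a little more programming. No new data are needed. Confidence intervals at month 12 will be somewhat wider than under LOCF, which reflects the information actually collected.
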